## Abstract

**Background:**

Pain and fatigue are persistent problems in people with rheumatoid arthritis. Central sensitisation (CS) may contribute to pain and fatigue, even when treatment has controlled inflammatory disease. This study aims to validate a self-report 8-item questionnaire, the Central Aspects of Pain in Rheumatoid Arthritis (CAP-RA) questionnaire, developed to measure central pain mechanisms in RA, and to predict patient outcomes and response to treatment. A secondary objective is to explore mechanisms linking CS, pain and fatigue in people with RA.

**Methods/design:**

This is a prospective observational cohort study recruiting 250 adults with active RA in secondary care. The CAP-RA questionnaire, demographic data, medical history, and patient reported outcome measures (PROMs) of traits associated with central sensitization will be collected using validated questionnaires. Quantitative sensory testing modalities of pressure pain detection thresholds, temporal summation and conditioned pain modulation will be indices of central sensitization, and blood markers, swollen joints and ultrasound scans will be indices of inflammation. Primary data collection will be at baseline and 12 weeks. The test-retest reliability of CAP-RA questionnaire will be determined 1 week after the baseline visit. Pain and fatigue data will be collected weekly via text messages for 12 weeks. CAP-RA psychometric properties, and predictive validity for outcomes at 3 months will be evaluated.

**Discussion:**

This study will validate a simple self-report questionnaire against psychophysical indices of central sensitization and patient reported outcome measures of traits associated with CS in a population of individuals with active RA. The application of this instrument in the clinical environment could provide a mechanism-based stratification tool to facilitate the provision of targeted therapy to individuals with pain and fatigue in RA, alongside treatments that target joint inflammation.

**Trial registration:**

Clinicaltrials.gov NCT04515589. Date of registration 17 August 2020.

**Supplementary Information:**

The online version contains supplementary material available at 10.1186/s41927-021-00187-2.

## Background

Rheumatoid Arthritis is a (RA) chronic autoimmune inflammatory disease affecting hands, feet and other joints. RA typically presents with pain, joint stiffness, and fatigue. It may be associated with extra-articular inflammation affecting, for example, lungs or eyes [1]. RA runs a relapsing and remitting course through the lifetime of an individual. There is currently no cure, but inflammatory disease can usually be controlled using conventional or biologic Disease Modifying Anti-Rheumatic Drugs (DMARDs). New treatment regimens incorporating early intensive DMARD treatment have contributed to improving quality of life of people with RA.

DMARDs produce and sustain remission of inflammatory disease for many people, but, even then, persistent pain and fatigue can remain major problems. On average, pain incompletely improves after DMARD therapy, with 80% of people who considered their disease to be well controlled continuing to report pain [2]. The prevalence of clinically important pain among people with sustained RA disease remission longer than 1 year is about 12% [3]. About 40% of patients with well controlled inflammatory disease reported persistent fatigue [4, 5].

Pain and fatigue in RA arise from complex and overlapping mechanisms involving inflammation, structural joint changes, central and peripheral pain processing, as well as psychosocial factors, health beliefs and illness perceptions [6, 7]. In RA, pain results from interactions between multiple mechanisms in the peripheral and central nervous systems. Individuals with RA pain describe it as aching or gnawing suggesting a nociceptive pain, and some describe it as ‘shooting’ or ‘burning’, which is characteristic of neuropathic pain [6]. RA pain may have nociplastic features, described as widespread, and without evidence of commensurate tissue or nerve damage [8]. Nociplastic pain may be due to central sensitization [9, 10]. Central sensitization is a phenomenon characterised by increased responsiveness of nociceptive neurons in the central nervous system to their normal or subthreshold afferent input. CS may be associated with fatigue independent of pain [11], although people with Chronic Fatigue Syndrome often experience widespread pain [12, 13], and people with fibromyalgia experience chronic fatigue.

Central mechanisms are thought to drive pain and fatigue in the presence of well controlled inflammatory disease. The disease activity score in 28 joints (DAS28) is a specific quantitative clinical index to assess and monitor disease activity in RA [14] and CS may increase patient-reported components of DAS28 - tender joint count (TJC) and visual analogue scores (VAS), worsening the DAS28 score in the absence of concordant inflammation [15]. In these circumstances misclassification of active disease could result in increased use of DMARDs, exposing people to the risk of adverse events without real prospect of benefit [16]. Too narrow a focus on suppressing inflammation can displace the introduction of adjunctive treatments that might reduce central sensitisation and improve long-term pain and fatigue in RA.

Current RA treatment guidelines adopt a ‘one size fits all’ approach to pain management, mainly targeted at nociceptive pain [17]. However, different pain mechanisms represent different targets for pain management and their measurement might permit stratified or precision treatment delivery to alleviate pain in people with RA. Furthermore, available evidence describes a heterogenous RA population with varying prognosis and treatment responses in terms of disease activity, pain, fatigue, functional limitations, and psychological distress [18–22]. Distinct pain mechanisms as well as heterogenous symptom response presents an opportunity for targeted interventions for symptom control e.g. people with persistent pain due to resistant joint inflammation might benefit from a change in DMARD strategy, whereas those with pain driven by central mechanisms might better benefit from treatments that target the central nervous system.

Several research studies have demonstrated an association between central pain mechanisms and persistent and severe pain in musculoskeletal conditions [23–26] A stratification tool which identifies people with central sensitisation could improve the treatment of RA pain. Central pain mechanisms can be assessed using a variety of methods, including quantitative sensory testing (QST) [27–29] and self-report questionnaires [23, 30].QST includes several modalities that assess different aspects of central pain processing [27]. Although QST shows promise as a stratification tool, its application in clinical settings is limited by logistic issues such as requiring face to face contact with a trained practitioner and test duration [28, 31]. Questionnaires permit economical assessment with relative ease and are suitable for use with large populations and in busy clinical settings. Questionnaires that can assess central pain mechanisms should, therefore, be more amenable than QST for standard applications in clinics and in research.

A single page 8 item questionnaire, Central Aspects of Pain in the knee (CAP-knee) was designed and validated as a measurement and classification tool for central pain augmentation in people with knee pain. This self-report tool measures 8 characteristics strongly associated with central pain mechanisms and predicts 1-year pain outcomes in people with knee pain [23]. The Central Aspects of Pain in RA (CAP-RA) is a minor adaptation of the CAP-knee questionnaire for use in a RA population. This study aims to further develop and validate the new self-report 8 item CAP-RA questionnaire for measuring central pain mechanisms in RA.

### Objectives

The primary objective is to:
to optimise and establish the psychometric properties of CAP-RA and

Secondary objectives are to:
measure the ability of CAP-RA to identify people with pain that is augmented by central mechanisms, are destined to have poor pain outcomes despite modern therapy directed at joint inflammation.Investigate factors associated with worse RA pain or fatigue at baseline and 3 months follow upCompare the performance of CAP-RA to other predictors of pain outcomesDerive CAP-RA scoring recommendations for stratification in clinical trials and in clinical practiceExamine associations between pain, central sensitization and fatigue in RA.Examine the short-term course of pain and fatigue in RA

## Methods/design

### Study design and setting

CAP-RA is an observational prospective study based in secondary care. Adults with RA who meet the study inclusion criteria will be recruited through secondary care rheumatology services (Sherwood Forest Hospitals NHS Foundation Trust; SFH). Participants will undergo clinical assessments, blood tests, ultrasound scans and complete the study questionnaire booklet at baseline, and 12 weeks later. A consecutive sample of participants will in addition complete the CAP-RA questionnaire 1 week after the baseline visit.

### Ethical considerations and study sponsor

The study submitted to the national integrated research application system (IRAS) and was reviewed and approved by the North of Scotland Research Ethics Committee (1) (reference no: 20/NS/0036) and will be performed in accordance with the UK policy framework for Health and Social Care Research, 2018, principles of good clinical practice and Helsinki Declaration. A SPIRIT 2013 statement checklist [32] is included in supplement 1. The CAP-RA study sponsor is the University of Nottingham (which supervises data management procedures, ethics amendment processes/dissemination, and study stopping guidelines) and the current protocol is version 1.2,18/08/2020. Samples of all study related documents including consent forms and participant communication are also included in supplement 2 and 3.

Informed consent will be sought and confirmed through a signed consent form at the start of the first study visit before commencing study procedures. Participants would be explicitly informed that partaking in the study would not affect the participant’s entitlements, treatment, or care during the study or in the future; and would not require or preclude participation in other research projects. Details about how to report study concerns or medical issues are also provided.

### Public and patient involvement and engagement

People with RA and members of the public were involved in the conceptualization and design of the study. The original CAP-knee questionnaire was developed in conjunction with patients and members of the general public. The minor wording adjustments to the CAP-knee questionnaire to suit a RA population were undertaken jointly by researchers ([name], [name], [name]) and patients through face to face meetings and by email. In addition, the CAP-RA study steering committee charged with overall management of the study comprises researchers and people with RA. The steering committee is charged with monitoring all aspects of study and ensuring that study conduct adheres to the study protocol and timescales.

Participants will be updated on research progress through newsletters. Research findings will be disseminated though multiple routes, such as spoken presentations, conference abstracts, online and in academic publications.

### Participants

Inclusion criteria: All of the following
Adults aged 18 years and aboveSatisfy the European League Against Rheumatism (EULAR) criteria for RA [33]Have active RA, as defined as DAS28 ≥ 3.2 at the baseline visitPain levels > 3 on a 0 to 10 numerical rating scale where 0 = no pain and 10 = worst imaginable pain.Ability to give informed consent

Exclusion criteria: Any of the following -
Unable to give informed consentInsufficient understanding of spoken or written English to comply with the requirements of the study protocol.Unable or unlikely to complete the proposed 12-week study follow up (e.g moving house, terminal diagnosis, current or planned pregnancy).Active co-morbidity (e.g uncontrolled diabetes mellitus, cancer, infection) requiring changes in medical treatment at baseline.Major active psychiatric condition (e.g major depression)Inability to meet the requirements of clinical assessments

### Recruitment

Participants will be recruited from secondary care. Outpatient records will be screened by a member of the clinical care team, and eligible participants will be contacted by letter and invited to join the study. The study will be publicised in posters placed in public areas within clinics/hospitals. Additionally, members of the research team will recruit participants via face:face discussions in Rheumatology outpatient clinics in accordance with local policies.

### Study regimen

The baseline and 12-week study visits will be held in a private clinic room. At the baseline visit, the participant’s eligibility will be verified, and informed consent will be obtained. The baseline and 12-week study assessments will have identical data collection protocols. A time window of 12–16 weeks will be acceptable for the follow up assessment. At 1 week after baseline assessment, a subset of 80 people will be invited to complete and return a postal questionnaire consisting of only the 8-item CAP-RA questionnaire to examine test-retest reliability. For the study duration, participants may opt-in to receive and respond to SMS text messages asking about weekly pain and fatigue levels. The study regimen is described in Fig. 1.

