#### Additional data collection

The CAP-RA questionnaire will, in addition, be mailed for completion by 80 consecutive participants 1 week after the baseline visit, to assess test-retest reliability.

The course of fatigue and pain will be assessed by sending participants weekly SMS text messages at approximately the same time each week, with the question “On a scale of 0 – 10, with 0 indicating no pain, and 10 indicating the worst imaginable pain, how would you rate your pain during the past week? Please respond to this message with a number. Thank you”. The equivalent question wording will be used to ask about weekly fatigue.

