### Sample size considerations

The overall study sample size has been calculated to determine the structural validity of the instrument using Rasch analysis. Our Rasch model assumes that item calibrations are within ±½ logit from stable values, with a 99% confidence interval. This gives an overall sample size of between 108 and 243, best to poor targeting [64]. We expect 200 participants will complete the study, from a sample of 250 participants. This is in keeping with COSMIN recommendations for Rasch analysis [56–58].

For longitudinal analysis over 12 weeks, we predict that *n* = 200 people will complete both study visits. The power calculation for a linear multiple regression with CAP-RA plus 5 baseline covariates (each assumed to have a correlation coefficient of 0.15 with the 12-week pain) yielded a sample size of *n* = 164 for α = 0.05 and power = 0.95.

Seventy-seven participants are required for the reliability study to estimate an ICC of 0.8, with 2 ratings, alpha of 0.05, 80% power, and a lower limit ICC not less than 0.6. Sample size calculation was implemented in R using “ICC.sample.size package” [65, 66].

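### Eighty postal retests for 77 required pairs leave a margin of three forms, with no stated return rate or top-up rule; the effect is moderate, and the 77 does not follow from the printed inputs

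*Protocol article*

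**What the plan says.** The number approached is given twice in the Protocol article. Study regimen says that "a subset of 80 people will be invited to complete and return a postal questionnaire", containing only the eight CAP-RA items. Additional data collection says that the form will "be mailed for completion by 80 consecutive participants 1 week after the baseline visit".

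The number needed is given under Sample size considerations: "Seventy-seven participants are required for the reliability study to estimate an ICC of 0.8". The calculation assumes that each person is rated twice, sets power at 80% and alpha at 0.05, and takes 0.6 as the limit below which the ICC should not fall. Whether alpha is one- or two-sided is not stated.

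For the main sample the same section allows for loss: "We expect 200 participants will complete the study, from a sample of 250 participants". Its longitudinal paragraph explains the 200 as those who "people will complete both study visits".

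Statistical analysis treats a test-retest ICC of at least 0.70 as acceptable. It lists reliability and measurement error among the psychometric properties that make up the primary objective.

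**The concern.** A test-retest ICC uses only complete pairs. If 80 forms go out and 77 usable ones are needed, the plan tolerates three that are unreturned, late or incomplete. That is thin for an unsupervised postal form, and the article fixes both numbers without a return rate to connect them. The main sample, by contrast, carries an explicit allowance for loss.

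At stake is the precision of the ICC, the standard error of measurement and the smallest detectable change. These belong to the primary objective, and this retest is the only data described for them.

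**Working it through.** **Inputs.** From the article: 80 mailed, 77 required, true ICC r1 = 0.8, lower limit r0 = 0.6, k = 2 ratings, alpha 0.05, power 80%, acceptability value 0.70, and 200 completers of 250. Assumed: the postal return rate, which the article does not give (80% to 95% shown), and a two-sided alpha except where noted.

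**1. The plan's own figure.** The usual sample size for testing an ICC is

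n = 1 + 2k(z_α + z_β)² / [(k − 1)(ln C)²], with C = [1 + k·r0/(1 − r0)] / [1 + k·r1/(1 − r1)].

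Two-sided 0.05 and 80% power give (1.960 + 0.842)² = 7.849. With k = 2 the numerator is 4 × 7.849 = 31.40.

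- r0 = 0.60: C = 4/9 = 0.4444, ln C = −0.8109, n = 1 + 31.40/0.6576 = 48.7, so 49 (one-sided: 38.6, so 39).
- r0 = 0.65: C = 0.5238, ln C = −0.6466, n = 1 + 31.40/0.4181 = 76.1, so 77 (one-sided: 60.1, so 61).
- r0 = 0.70: C = 0.6296, ln C = −0.4626, n = 1 + 31.40/0.2140 = 147.7, so 148 (one-sided: 116.6, so 117).

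The printed lower limit of 0.6 does not reproduce 77. Of these combinations, only 0.65 with a two-sided alpha does. A Fisher-z version agrees (49.2 at 0.60, 76.6 at 0.65). A large-sample variance version gives smaller numbers still (26.4 and 46.2).

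**2. Return needed.** 77/80 = 96.25%. For the 49 pairs that the printed inputs need, it is 49/80 = 61%.

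**3. Chance of at least 77 usable forms from 80** (binomial):

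| Assumed return | Expected pairs | P(at least 77) |
|---|---|---|
| 80% | 64 | 0.003% |
| 85% | 68 | 0.13% |
| 90% | 72 | 3.5% |
| 95% | 76 | 43% |

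**4. Power at the resulting sizes** (exact one-way F test, true ICC 0.8, two-sided 0.05):

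| Pairs | Against 0.60 (printed) | Against 0.65 (inferred) |
|---|---|---|
| 49 | 80% | 61% |
| 64 | 89% | 72.5% |
| 72 | 93% | 77.5% |
| 77 | 94% | 80% |

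**5. Precision.** For an observed ICC of 0.8, F = 1 + 2(0.8)/0.2 = 9. The exact 95% interval is 0.703 to 0.868 with 77 pairs and 0.691 to 0.873 with 64. The lower bound moves by 0.012, from just above 0.70 to just below it.

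**6. Mailings needed if 77 stands.** 77/0.90 = 85.6, so 86; 77/0.80 = 96.3, so 97.

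**The case against.** The strongest reply is that the design aim as printed is not at risk. Detecting 0.8 against 0.6 with 80% power takes about 49 pairs. Eighty mailings at an 80% return would deliver at least 49 with probability above 99.9%. This stands, and it limits the consequence under the printed inputs.

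A reader might infer that the study's own 20% loss applies to the retest, so that 64 pairs are to be expected and 77 will almost certainly be missed. The article does not support this. The 20% concerns completing the study, with two full assessment visits over at least 12 weeks. The retest is one short form, one week after baseline. The 20% is only a proxy, and a 95% return would leave a 43% chance of reaching 77.

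A reader might also take the power against 0.70, about 45% at 64 pairs, as the price of too few mailings. It is only 52% at the full 77, so the shortfall accounts for about 7 points. The article uses 0.70 as an acceptability value and does not plan a test against it.

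The 72.5% needs the inferred 0.65 and a two-sided alpha. With a one-sided 0.05, power at 64 pairs against 0.65 is 82%.

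Finally, neither section says that mailing stops at 80, and the wording under Additional data collection could be read as 80 completions. Study regimen, however, speaks of 80 invited. Reminders may well be left to the full protocol, but the two printed numbers still leave only three forms between them.

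**Conclusion.** The point holds as a mismatch between two printed numbers: 80 approached, 77 required, and no return rate or top-up rule to connect them. The stated requirement would more likely than not be missed at a 95% return, and would very probably be missed at 90% or below. These return rates are assumptions.

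The consequence is moderate and depends on which input is right. With the printed limit of 0.6, even 64 pairs keep power at 89%, so the procedure is adequate and 77 is more than the stated aim needs. With 0.65, which reproduces the 77 but appears nowhere in the article, power at 64 pairs falls to 72.5% against the 80% planned. The loss of precision is small, although at an observed ICC of 0.8 it moves the lower confidence bound across 0.70. The documents do not support a claim that the reliability study will fail.

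**What to change.** First reconcile the 77 with the 0.6 lower limit: correct whichever is misprinted and state whether alpha is one- or two-sided. Then replace the fixed 80 invitations by a rule such as: consecutive enrolled participants are mailed the retest until the reconciled number of complete pairs has been returned within a stated window.

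If 77 stands, expect about 86 mailings at a 90% return or 97 at 80%, which is 6 to 17 more than planned and well within the 250 recruited. These are expected numbers; the rule itself secures the target whatever the return rate proves to be. If the reconciled number is 49, 49/0.80 = 61.25, so 62 mailings would do at an 80% return, and the planned 80 already cover it.

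The cost is a few more one-page mailings and a sentence or two in the protocol, with no added visit.

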**Fig. 1 Fig1:**
[figure not shown]
Schematic diagram of CAP-RA study regimen

### Data collection

#### Questionnaire

The study questionnaire booklet was developed using validated instruments as well as the newly designed CAP-RA questionnaire.

RA pain will be measured using 0–10 numerical rating scale and fatigue [34], using the Bristol RA Fatigue Scale (BRAFS) multidimensional questionnaire [35].

Traits associated with central pain mechanisms will be assessed using the CAP-RA questionnaire and the Central Sensitization Inventory short form-9(CSI-9) [36, 37]. Information on neuropathic-like pain will be collected by a modified painDETECT questionnaire [38]. The waveform and pain intensity questions were removed as these are not included in the neuropathic pain score, and questions were reworded as statements for easy readability. Additionally, the questionnaire will utilise, the pain catastrophising scale (PSC) [39], and the Bristol RA Fatigue Scale (BRAFS) multi-dimensional questionnaire [35]. Depression and anxiety will be measured using the Hospital Anxiety and Depression Scale (HADS) [40]; functional ability,; and sleep, by the Athens Insomnia Scale (ASC) [41]. Cognitive function will be measured using the Cognitive Failures Questionnaire (CFQ) [42].

The questionnaire will also address conditions, treatments and outcomes that are associated with central pain mechanisms and fatigue. The presence of fibromyalgia will be classified using pain distribution from a self-completed whole-body manikin, to derive the Widespread Pain Index (WPI), and Symptom Severity Score (SSS) [43, 44]. Disability and physical activity will be assessed with the Health Assessment Questionnaire (HAQ) [45] and the short International Physical Activity Questionnaires (IPAQ) [46] respectively. Demographic characteristics will be recorded, and comorbidities required to calculate the Rheumatic Disease Co-Morbidity Index (RDCI) will be assessed [47]. A detailed medication history will be collected, including common medications used to manage RA, common pain medications e.g. nonsteroidal anti-inflammatory drugs (NSAIDs), paracetamol.

